### Sample size and power calculations

#### Eczema

From our previous study the hazard ratio for eczema, for HN001, based on the data at 6 and 12 months, was 0.39, with 12.3 % of infants having eczema at either 6 or 12 months. With a sample size of 200 in each group and 13 % drop-out rate, 43 babies are expected to be assessed as having eczema. Using the sample size formula from Therneau and Grambsch [65], the study will have 87 % power at the 5 % level of significance.

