#### Assessment of primary outcomes

##### Infant eczema

After withholding topical creams and oils for 24 h the prevalence of eczema in infants is assessed at 6 and 12 months using the UK Working Party’s Diagnostic Criteria for atopic dermatitis [69] which is adapted for infants under 12 months [9]. All research staff members undertake online training in the application of this tool. Eczema is assessed as present at each visit if there is a history of scratching or rubbing and two or more of the following occurring since birth or the previous visit: (1) a history of involvement of outer arms or legs, (2) a history of a generally dry skin, or (3) visible eczema present on the cheeks or outer arms or legs with no axillary involvement. Eczema severity is assessed at the same time points using SCORAD [66] with staff recording any region of greater than or equal to 1 cm diameter that meets the skin change criteria [69] for eczema. For the purpose of consistency between the UK Working Party’s definition of atopic dermatitis and SCORAD, papulation is considered a surface change when using these tools.

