### Data analysis

An intention-to-treat analysis will be used to assess the effect of HN001 on the 12 month cumulative prevalence of eczema and SCORAD ≥10 using hazard ratios from a Cox’s proportional hazards model, and the point prevalence of atopy at age 12 months using relative rates and a chi-squared test. Chi-square test will also be used to compare the proportion in each study group with detectable levels of immunological markers in breast milk and for those with detectable levels, t-tests will be used to compare the groups if the data is log-normally distributed. If the data is not log-normally distributed a Wilcoxon Rank-Sum test will be used. Where there are important differences between groups, these variables will be added to the models to assess whether these variables mediate any effect of HN001 on eczema and/or atopic sensitisation (using a generalised linear model with a log link and binomial distribution). The association of HN001 with the presence of GDM, BV and GBS will be assessed using relative rates and chi-squared tests. EPDS and State Anxiety Inventory will be compared with a Wilcoxon Rank-Sum test. The effect of weight gain will be investigated as an intermediate variable by adding it to the model (a generalised linear model with a log link and binomial distribution) in the GDM analysis. Any baseline differences that occur will be adjusted for. If commercially available non-study probiotics have been used, a sub-group analysis will be performed after excluding this group, which we do not expect to be large. Reasons for withdrawal from the study will be recorded and examined for differences between study groups. Adjustment will be made for differences in antibiotic use between study groups. SAS version 9.4 will be used.

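### The 87% eczema power is correct for the events formula used, but that formula is optimistic at a hazard ratio of 0.39; the planned Cox analysis has about 83–84%

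*Protocol article*

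**What the plan says.** The eczema paragraph of the sample size section (protocol article) draws its inputs from the group's previous trial. It reports that "the hazard ratio for eczema, for HN001, based on the data at 6 and 12 months, was 0.39". It puts the share of infants affected at one visit or the other at 12.3%. Starting from 200 women per group and allowing for 13% loss, it then states that "43 babies are expected to be assessed as having eczema". It cites a textbook sample size formula and concludes without qualification that "the study will have 87 % power at the 5 % level of significance".

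The section on infant eczema says that "the prevalence of eczema in infants is assessed at 6 and 12 months", and that SCORAD is recorded at the same visits. The data analysis section plans "hazard ratios from a Cox" proportional hazards model for 12-month cumulative eczema and for SCORAD of 10 or more, using SAS 9.4. The article gives no tie method, test statistic or sidedness.

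**The concern.** Eczema is the first-listed primary outcome, and its power figure is part of the case for 200 women per group. Events formulas of this kind take the variance of the log hazard ratio as it would be if events fell equally in the two arms. That is accurate for modest effects. At a hazard ratio of 0.39 the treated arm contributes far fewer events than the control arm, so the true variance is larger and the formula overstates power.

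A smaller, separate matter is that eczema status is learned at only two scheduled visits. If time is taken as the nominal visit, the events are heavily tied, and the way a Cox model handles ties then has a small effect on the test and the estimate.

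**Working it through.** **Inputs** (eczema paragraph): hazard ratio 0.39; 12.3% with eczema; 200 per group; 13% drop-out; 5% level. Assumptions: two-sided test; 12.3% is the rate over both arms (the reading that yields 43 events); proportional hazards; drop-outs contribute no events.

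**1. Reproducing the plan's figures.**
- Assessed infants: 400 × 0.87 = 348, or 174 per arm.
- Events: 348 × 0.123 = 42.8, rounded to 43.
- Events formula with equal allocation: power = Φ(√(d/4) × |ln HR| − 1.96). With d = 43 and |ln 0.39| = 0.942 this is Φ(3.279 × 0.942 − 1.96) = Φ(1.127) = 87.0%.

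Both stated figures reproduce. The article does not print the formula, but the match indicates that it is of this type.

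**2. Where the formula is optimistic.**
- Let p be the control risk. The HN001 risk is 1 − (1 − p)^0.39. Setting the mean of the two to 12.3% gives 17.4% for control and 7.2% for HN001.
- Expected events: 174 × 0.1741 = 30.3 and 174 × 0.0719 = 12.5.
- Variance in the formula: 4/42.8 = 0.093.
- Variance at these counts: 1/30.3 + 1/12.5 = 0.113, about 21% larger.

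Two closed-form alternatives show the direction:
- Wald with variance 0.113: Φ(0.942/√0.113 − 1.96) = 80.0%.
- Freedman's formula with 43 events: Φ(√43 × 0.61/1.39 − 1.96) = 82.1%.

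**3. Simulating the planned analysis.** 174 per arm; events recorded at 6 or 12 months; 20,000 trials for each of 30%, 50% and 70% of the hazard falling before 6 months (the split is not given and made little difference). The exact-time comparison used 8,000 trials.

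| Analysis | Wald | Likelihood ratio | Score |
|---|---|---|---|
| Cox, two visits, Efron ties | 83.2–83.3% | 84.3–84.5% | – |
| Cox, two visits, Breslow ties | 81.2–81.6% | 82.4–82.8% | – |
| Log-rank, two visits | – | – | 84.0–84.2% |
| Cox, exact event times, no ties | 82.6% | 83.8% | 83.6% |

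A complementary log-log model (3,000 trials) gave 82.5% by Wald and 83.6% by likelihood ratio.

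**4. Separating the two causes.** With exact event times power is still about 83–84%, so the loss from 87% is already there before any grouping into visits. Two visits with Efron ties cost nothing. Breslow ties would cost a further 1 to 2 points.

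**5. What Breslow ties would do.** In a null simulation at the same event rate, type I error was 3.8% (Wald) and 4.3% (likelihood ratio) with Breslow, against 4.5% and 5.0% with Efron. With a true hazard ratio of 0.39, the median estimate was about 0.40 with Breslow and 0.39 with Efron.

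**The case against.** The best defence is that nothing is miscalculated. The article names its method and gives its inputs, and 87% follows from them. That stands, so a reader who inferred an arithmetic error would be wrong. What remains is that the article states the power of the study without calling it approximate, and the planned analysis does not reach it under the same inputs.

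A reader might also blame the two visits. Step 4 does not support this. Nor does the article commit to Breslow ties: it names no tie method, and an analysis plan not shown here may settle it. It also does not say whether time is nominal visit or actual age. The Breslow results are therefore conditional, and the missing tie method is not a defect of the article.

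The strongest numerical objection concerns drop-out. Infants seen at 6 months and lost later still contribute to a Cox model. Suppose, as an extreme case, that all 52 drop-outs are seen at 6 months and half the hazard falls before then. About 3 more events accrue, and power with Efron ties rises to about 86–87%, or a little more if more of the hazard falls early. This narrows the gap, but it departs from the 43 events on which the article bases its figure. With about 46.1 events the same formula would give Φ(√(46.1/4) × 0.942 − 1.96) = 89%, so it would still be optimistic.

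Finally, uncertainty about the true effect matters more than this approximation: at an illustrative hazard ratio of 0.45 the same formula gives about 74%. That is a fair reason to rate the point low.

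**Conclusion.** The point holds in a limited form. With 174 infants per arm, 12.3% overall and a hazard ratio of 0.39, the planned Cox analysis has about 83–84% power, not 87%; the chance of missing the assumed effect is about 16–17%, not 13%. The cause is a near-null approximation used at a large effect. Tie handling is secondary, worth 1 to 2 points and only if Breslow were used.

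The result rests on a two-sided 5% test, 12.3% as the rate over both arms, proportional hazards, and the article's own count of 43 events. A reader might infer that the trial is underpowered for eczema. The figures do not support that, because simulated power stayed above 80% in every variant. Severity is minor.

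**What to change.** Restate the eczema power as about 83–84%, or keep 87% and label it as the result of a large-sample events formula, with the simulated figure beside it.

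As a secondary step, specify for eczema and for SCORAD of 10 or more a method suited to two assessment times: Cox with Efron or exact ties, or a complementary log-log model with a visit term. Both target the same hazard ratio. This does not bring power back to 87%; it avoids the small avoidable loss and the slight pull of the estimate that Breslow ties would bring.

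The cost is one sentence in the sample size section and one line of analysis code. Sample size and data collection are unchanged.

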#### SCORing Atopic Dermatitis (SCORAD)

Our previous study [9] found a reduction in SCORAD [66] ≥10 from 22.9 to 12.8 % due to the probiotic intervention. With a sample size of 200 in each group and a 13 % drop-out rate, the study will have 69 % power at the 5 % level of significance.

#### Atopic sensitisation

In general, effects of probiotics on sensitisation have only been seen in a subset of children with allergic [16] or sensitised mothers [12]. Assuming 60 % of mothers are skin prick test positive and a reduction in the prevalence of atopy from 50 to 26 % among their children, as seen in the paper by Huurre et al. [12], with a sample size of 200 pregnant women (120 with mothers who are sensitised) in each group and 13 % drop-out rate our study will have 95 % power at the 5 % level of significance, for atopic sensitisation among the children of mothers that are skin prick test positive. A further analysis of the data from the study by Huurre et al. [12] shows that there is a four-fold increased risk of sensitisation in the sub-group without maternal sensitisation. Assuming a similar difference in risk dependent on mother’s atopic status, the study would have >99 % power to show an interaction effect.

#### Gestational diabetes mellitus

Assuming a GDM prevalence rate of 15 %, and based on the study by Luoto [31] which showed a 63 % reduction in prevalence of diabetes mellitus in pregnant women due to a probiotic intervention, with a sample size of 200 in each group and a 2.5 % drop-out rate the study will have 87 % power to detect a difference at the 5 % level of significance.

#### Bacterial vaginosis

We cannot locate any published data on the prevalence of BV in New Zealand women but international data suggest it is around 30 % [67]. A probiotic treatment RCT of BV by Anukam [42] found a 88 % cure rate (defined as normal nugent score and other markers of BV at 30 days post treatment) in the probiotic group and 40 % in the placebo group. Assuming a 30 % rate in the placebo group, and a similar probiotic effect resulting in a 6 % rate of BV in the probiotic group, the study will have >95 % power at the 5 % level of significance with a sample size of 200 in each group and 2.5 % drop-out rate.

#### Group B streptococcus

We are not aware of any studies of a probiotic treatment effect on GBS carriage on which to base power calculations but the New Zealand prevalence was reported to be 22 % in 1998-9 [46]. With a sample size of 200 in each group and a 2.5 % drop-out rate, the study will have 84 % power to detect a reduction to 11 % at a 5 % level of significance.

### Maternal postpartum depression and anxiety

The distribution of the Edinburgh Postnatal Depression Scale (EPDS) from Growing up in New Zealand Study [68] was used. With a sample size of 200 in each group and 13 % drop-out rate, using a Wilcoxon Rank-Sum test, the study will have 79 % power to detect a 26 % reduction in EPDS at a 5 % level of significance.

## Ethics

The study received ethical approval from the New Zealand Multi-region Ethics Committee (MEC/11/09/077). Prior to commencing the study, adult participants receive all the necessary information in relation to the study, and written informed consent is obtained. Women provide written informed consent on behalf of both themselves and their unborn child/infant.

### Study population

#### Pregnant women

English-speaking pregnant women who intend to breastfeed their infant are eligible to be enrolled in the study between 14 and 16 weeks gestation if either they or the unborn child’s biological father have a history of asthma or eczema treated by a doctor, or allergic rhinitis treated by a doctor or pharmacist. A woman is excluded if she: is under age 16, does not intend to stay in either of the study centers for the 18 months following enrolment, has a serious immunological disorder that suppresses immune function or is taking immune suppressant drugs, has known cardiac valve disease for which antibiotic prophylaxis is required when undergoing dental procedures, has a history of a transplant or human immunodeficiency virus, were on long-term of continuous antibiotic therapy, required in vitro fertilisation to establish the current pregnancy, has a pre-enrolment scan showing major fetal abnormalities, at the time of enrolment is using or intended to use probiotic drinks or supplements themselves or in their child, is participating in another randomised controlled trial, has a severe allergy to cow’s milk (as probiotic capsules may contain traces of milk), has previously participated in the study with an older child or is deemed unsuitable for study inclusion for any other medical reason. Any pregnant woman with pre-existing type 1 or 2 diabetes is eligible for the study but is excluded from the oral gestational tolerance test (OGTT) and gestational diabetes outcomes.

#### Infants

All infants born in the study are eligible for inclusion in study outcomes. In the case of multiple births, only the first-born infant will be included in the study.

#### Fathers

The biological father of the infant is invited to participate in a study visit to obtain some background data relating to their history of allergic disease, atopic sensitisation by skin testing and anthropometric measures. These data are being collected to enable examination of the relationship between paternal characteristics and infant growth, allergic disease and atopic sensitisation.

### Recruitment

A range of recruitment strategies are used to notify pregnant women about the study and to invite them to contact the study centres to discuss the study and be assessed for study eligibility. These include: enclosing study brochures in information packs routinely given to women by clinicians and midwives in early pregnancy, emailing employees of large organisations, using web-based approaches such as Facebook, arranging for sonographers and phlebotomists to hand out study brochures at the time of early scans and the first antenatal blood collection, radio advertising, newspaper articles as well as pamphlets and posters placed at hospitals, clinics, crèches, libraries and pharmacies and inviting clinicians (midwives, obstetricians and general practitioners) to refer women to the study.

Pregnant women who contact the study centres are screened for eligibility by phone and if eligible are invited to attend an enrolment visit at the study centre when they reach between 14 and 16 weeks gestation.

### Study intervention

#### Capsules

Study capsules containing *Lactobacillus rhamnosus* HN001 (6x10^9^ cfu) are manufactured by Fonterra Co-operative Group Ltd as previously described [9]. Shelf life is managed to ensure minimum viable counts of 6×10^9^cfu are maintained in the HN001 capsules. The placebo powder is corn-derived maltodextrin, manufactured by Grain Processing Corp. Oregon, USA and is supplied to Fonterra Co-operative Group Ltd by Salkat New Zealand Ltd, Auckland. Placebo capsules have identical appearance and smell to the probiotic capsules. Both probiotic and placebo powders are encapsulated by Alaron Products Ltd, Nelson, New Zealand and provided in opaque bottles. Quality and safety testing is performed to a pharmaceutical standard (Therapeutic Goods Act) by a registered external laboratory.

#### Randomisation process

Randomisation is managed by Fonterra Co-operative Group Ltd and concealed from all study staff and participants. Randomisation is stratified by study centre and performed in blocks of random lengths according to a computer-generated randomisation list. At enrolment, a research staff member assigns the woman the next consecutive study number and provides her with the appropriate capsules.

#### Capsule viability and compliance

All capsules are stored at 4° Celsius (°C) in the study centres and participants are advised to store the capsules in their home refrigerator. Written and verbal instructions regarding use and storage of capsules are provided to participants. Women are advised to take one study capsule daily from enrolment until 6 months after birth if breastfeeding, or to cease capsules before 6 month post birth if they have not breastfed for 24 h. To assess compliance, capsule bottles are collected at regular intervals and counts of remaining capsules are completed by an independent person. Samples of capsules returned from the field are tested to ensure that capsules have maintained their viability. As previously described [9], viable bacteria are counted using standard methods, and counts checked against samples of HN001 kept at 4 °C.

### Study assessments

Table 2 provides a summary of the study timeline and investigations. Women enrolled in the study are provided with a study calendar to assist them to prospectively record data relevant to the study questionnaires. Research staff members are trained in standardised administration of all study questionnaires and data collection procedures.

**Table 2 Tab2:** Study timeline and investigations

		14-16 Weeks Gestation	26-28 Weeks Gestation	35-37 Weeks Gestation	Birth	3-7 Days After Birth	Infant Age 3 Months	Infant Age 6 Months	Infant Age 12 Months
	Intervention: new bottle study capsules	✓ Intervention commences	✓			✓	✓	Intervention stops	
	Questionnaire	✓	✓			✓	✓	✓	✓
Objective measures and samples: Maternal									
	Vaginal swab (BV)	✓		✓					
	Vagino-rectal swab (GBS)	✓		✓					
	Anthropometry^a,b,c,d^	✓				✓		✓	✓
	Blood samples (OGTT and serum)		✓^e^						
	Faecal sample		✓						
	3 day food diary		✓						
	Cord blood and tissue				✓				
	Breast milk					✓			
	Skin prick test							✓Completed after birth	
Objective measures and samples: Infant									
	Anthropometry^a,b,c^					✓		✓	✓
	Eczema							✓	✓
	SCORAD							✓	✓
	Faecal sample								✓
	48 hour food diary								✓
	Buccal sample								✓
	Skin swabs								✓
	Skin prick test								✓
Objective measures and samples: Paternal									
	Anthropometry^a,b,c^					✓Completed at any visit after birth			
	Skin prick test					✓Completed at any visit after birth			

*BV* bacterial vaginosis, *GBS* group B streptococcus, *OGTT* oral glucose tolerance test, *SCORAD* scoring atopic dermatitis

^a^height/length ^b^weight ^c^head circumference ^d^waist circumference ^e^excluding women with pre-existing diabetes

Questionnaires collect a range of data including confounders (such as previous GDM, parity etc.), effect modifiers (such as use of antibiotics, yoghurt etc.), outcome data, and adverse events.

#### Assessment of primary outcomes

##### Infant eczema

After withholding topical creams and oils for 24 h the prevalence of eczema in infants is assessed at 6 and 12 months using the UK Working Party’s Diagnostic Criteria for atopic dermatitis [69] which is adapted for infants under 12 months [9]. All research staff members undertake online training in the application of this tool. Eczema is assessed as present at each visit if there is a history of scratching or rubbing and two or more of the following occurring since birth or the previous visit: (1) a history of involvement of outer arms or legs, (2) a history of a generally dry skin, or (3) visible eczema present on the cheeks or outer arms or legs with no axillary involvement. Eczema severity is assessed at the same time points using SCORAD [66] with staff recording any region of greater than or equal to 1 cm diameter that meets the skin change criteria [69] for eczema. For the purpose of consistency between the UK Working Party’s definition of atopic dermatitis and SCORAD, papulation is considered a surface change when using these tools.

##### Atopic sensitisation

Skin prick tests are performed using standardised protocols, (after relevant antihistamine withhold periods if needed) using Stallergenes 1 mm lancets (Antony, France), positive control (histamine 10 mg/ml), negative control (phenolated glycerol-saline), *Dermatophagoides pteronyssinus*, cat fur, five grass mix (cocksfoot, sweet vernal, rye, timothy and meadow grass), (Alyostal Stallergenes, Antony, France), egg white, peanut and cow’s milk (ALK- ABELLO, Madrid, Spain). Both biological parents are tested with positive, negative controls and aeroallergens only. Infants are tested at 12 months using both controls and all allergens. After application allergens are pricked vertically for 1 s, positive control wheals are measured at 10 min, and the negative control and all allergens are measured at 15 min to the nearest mm. The wheal size is calculated as the mean of the longest diameter and the midpoint perpendicular diameter. After the subtraction of any reaction to the negative control a mean wheal diameter of 3 mm or greater will be considered a positive reaction.

#### Assessment of secondary outcomes

##### Gestational diabetes mellitus

Women who are diagnosed with diabetes prior to 20 weeks gestation are excluded from the gestational diabetes outcomes for the study, as this diagnosis is likely to reflect pre-existing diabetes. Gestational diabetes outcomes are assessed at 26–28 weeks gestation, by a three time-point test 75 g oral glucose tolerance test (OGTT) recommended by international guidelines [25]. Preparation for the test include a 10–16 h pretest fast with instructions to avoid smoking during this time and during the test, and avoidance of exercise on the morning of the test. Participants remain in a resting state during the test which comprises of a baseline fasting blood sample, 75 g glucose load and blood samples at 1 and 2 h post load. An additional blood sample is collected at the time of the fasting blood test and this sample is separated and the serum stored at −80 °C for future analysis.

